**Fig. 3 Fig3:**
[figure not shown]
The flow diagram of the intervention describes the steps followed to carry out the intervention, as well as the two study conditions. Sessions for each condition will be also described. The sessions are held at the school and a teacher is present

#### Participants

The target population will be students between the ages of 14 and 18 enrolled in the third and fourth years of Compulsory Secondary Education (CSE), the first year of high school or intermediate training cycles of publicly affiliated Secondary Education Institutes (SEI) in Andalusia, equivalent to grades 9, 10, 11 and 12, respectively, in the United States. The inclusion criteria in the study for schools are: 1) Secondary School in Andalusia; 2) having access to the Internet; and 3) allowing the use of computers, mobile phones, or tablets to carry out the activity. The exclusion criteria for the students are: 1) having previously participated in a specific program for the prevention of cannabis use 2), having difficulties in the language of the program (Spanish) 3), not wanting to participate or not having parental consent to participate.

#### Selection and collection of samples

Contact will be made with all Andalusia schools that have students between the aged of 14 and 18 in their classrooms. According to the data provided by the Education Webpage of the Junta de Andalucía [50] (using the filters secondary education, intermediate vocational training, basic vocational education, and baccalaureate) 119 provincial capital schools can be approached. A member of the investigative team will call all schools. All information provided by telephone will also be mailed to schools interested in participating (program manual, manual summary, application management document, resolution of the Ethics Committee, active consent for parent’s form). This parent-consent form must be signed by parents through iPasen [51], which is the mobile application of the Department of Education and Sports of the Junta de Andalucía that allows communication between different members of the educational community (legal guardians, students, management positions and teachers). Some school nurses also assisted in recruiting schools, during the second batch of recruitment.

Weekly, members of the team will call the counselors of these centers to obtain their definitive participation. The randomization process will be carried out using the Research Randomizer computer software (Version 4.0) [48]. Over the phone, agreements will be made on the dates for the sessions. During the first session, a member of the research team will be present face-to-face or online, so that the teacher who will be present with the students in the next session knows how the platform works (although previously the teacher has been able to use the platform to find out how does it work).

#### Experimental condition (Alerta Cannabis Program)

Participants will complete the Alerta Cannabis intervention (described in Sect.Intervention characteristics).

#### Control condition

Participants in the control condition only will complete one initial questionnaire (pre-test) and two follow-ups (post-test) at six and twelve months.

### Measurements

#### Sociodemographic Variables

They will include gender (female/male), age (in years), parental educational level (none, primary, secondary, university, not knowing), student’s academic year, religion (Catholic, Protestant/Evangelical, Muslim/Islamic, other religion, and no religion) and nationality (Spanish, other). To assess socioeconomic status, the Family Affluence Scale [52] will be used, which consists of six different questions (Does your family own a car, van, or truck? Do you have a bedroom? How many times did your family travel outside of Spain last year on vacation? How many computers (including laptops and tablets, excluding game consoles and smartphones) does your family have? Does your family have a dishwasher at home? How many bathrooms (rooms with a bath/shower or both) are in your house [53–56]. The family Apgar test will be chosen to measure the self-perception of the family’s functional status. It will consist of five questions answered using a three-point Likert-type scale, assessing adaptability or mobilization of resources (Are you satisfied with the help you receive from your family when you have problems? ), participation or cooperation (Do you talk at home about the problems?, What do you have? ), development or growth (Are important family decisions discussed together at home? ), resolve or ability to spend time with a family member (Are you satisfied with the time you spend with your family?) [41].

#### Primary and secondary results: cannabis use and intention to cannabis use

We will measure the frequency and intention of cannabis use. The frequency of cannabis use will be measured with the questions used by the ESTUDES survey [57], which include the days the adolescent has consumed cannabis (hashish/marijuana) in their life, in the last 12 months, and in the last 30 days. In addition, the number of joint consumptions per day will be measured in the last 30 days. We will ask two questions to measure cannabis use intention: Do you intend to use cannabis in the future? Do you intend to use cannabis next year?

#### Motivation factors

To study the motivational factors associated with cannabis use, we based ourselves on previous studies by the team [25].

The advantages and disadvantages of cannabis use will be explored through nine items scored on a five-point Likert scale (1 = strongly agree, 5 = strongly disagree). For example, marijuana use produces family problems (advantage), or cannabis use relaxes me (disadvantage).

Regarding social influences, social modeling will be assessed by asking participants how often people in their environment (i.e., parents, brothers/sisters, friends) use cannabis (1 = never; 5 = always). The social norm will be assessed by asking participants what people around them (that is, parents, brothers/sisters, friends) think about whether the adolescent should use cannabis (1 = definitively should not use cannabis; 5 = definitively should use cannabis). Social pressure will be assessed by asking participants if they have felt pressured to use cannabis by people around them (that is, parents, brothers/sisters, friends) about whether or not they should use cannabis (1 = never; 5 = always). For example, I have felt pressured to use cannabis for my sister.

Self-efficacy will be measured with ten items. Each item assesses whether participants feel confident about not using cannabis in a certain difficult situation (situations that would normally trigger cannabis use, for example, “How difficult or easy is it for you not to use cannabis, if you are at a party and your friend offers you a joint”?). We use a five-point scale (1 = very difficult; 5 = very easy).

### Ethics procedure and approval

The voluntary nature and confidentiality of the data provided by the participants are guaranteed, based on Royal Decree-Law 5/2018, of 27 July on the Protection of Personal Data and the European Data Protection Regulation [58]. Informed consent will be requested both from parents and from the adolescent to participate in the project. This study has been designed in accordance with the Declaration of Helsinki and has the approval of the Andalusian Bioethics Committee (Code 2162- N -20) and the approval of the data management protocol for Alerta Cannabis by the University of Seville.

## Evaluation phase

### Effectiveness and process evaluation

General descriptive statistics will be used to describe the baseline characteristics of the participants. Since the students will be nested within a class in the study and classes will be nested within schools, to examine the predictors of dropout versus non-dropout, a multilevel logistic regression analysis will be conducted. In addition, a multilevel approach will be used to assess the effects of the intervention on the behavior of cannabis use. The first level will be repeated measures within the participants (baseline and two follow-up measurements), the second level will be the student, the third level is the class, and the fourth level is the school.

Baseline cannabis will use behavior and the demographic variables described above will be included as covariates. To select significant predictors and interactions, a backward deletion procedure (a = 0.05) will be used, with the restriction that predictors will not be removed from the model if they were involved as terms.

To study the predictors of adherence, we will also analyze the associations between the potential characteristics (i.e., gender, age, academic course, religion, nationality, family wealth score, Apgar score, and cannabis use at baseline) on the one hand, and participation in the intervention (i.e., adherent or not) through the number of sessions attended by participants at schools on the other.

Finally, for the process evaluation, a descriptive analysis will be performed using chi-square tests to examine differences between males and females and between cannabis users and non-users. We use SPSS Statistics for Windows, version 26.0 (IBM Corp.), for these analyses.

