#### Intervention characteristics

This program will be implemented during the academic year during school hours. It is intended for adolescents between the ages of 14 and 18. It consists of four half-hour sessions given once a week or every two weeks by the professors, except for the first, where, in addition to the professors, a member of the research team will be present face-to-face or online, to explain what the course consists of program and how to use the application. Teachers will previously receive all the information about the program through the school counselor, they will even be able to register and use the platform if they want to explore it beforehand. The program is designed to be self-administered, individualized, and personalized, and is very intuitive. The Alerta Cannabis intervention will consist of preventive messages and personalized information on the benefits of not using cannabis, based on the I-Change model. In the first intervention session, the knowledge and risk of cannabis use will be addressed (level of danger, susceptibility, and severity), as well as the pros of cannabis use. In the second session, the cons of cannabis use (emphasizing the negative aspects of its consumption to foster an attitude of rejection of it) and the social model will be worked on (helping adolescents to choose the models they consider most appropriate and encouraging them to seek the support of friends and family who do not use cannabis). In the third session, social norms (helping adolescents to deal with the perceived approval of cannabis use in their environment as well as to choose real relationships that can help them avoid their use) and social pressure (avoiding the influence of people who consume cannabis in their environment) will be worked on. The fourth session is a reinforcement session in which all the aforementioned concepts are worked on and, in addition, the challenge of not consuming cannabis will be proposed to the participants. To evaluate the challenge, the participants who accept it will receive an e-mail asking them to answer whether or not they have been able to overcome the challenge. In all sessions, skills (self-efficacy and action plans) will also be worked on to reject cannabis.

Before starting the first session of the intervention, participants will have to complete an initial questionnaire (pre-test) and two follow-up questionnaires (post-test at six months and twelve months).

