### Implementation phase

#### Study design

A two-arm cluster-randomized controlled trial (CRCT) will be designed, with an experimental condition (EC) and a control condition (CC) condition will be randomized at the school level. An initial assessment (pretest) and two assessments (post-test) will be performed at six and twelve months. The allocation ratio will be 1:1 using an online randomization system [48] (Fig. 3). Randomization will be performed by a member of the research team. Randomization will be carried out in batches, since after previous studies we have verified that not all schools confirm their participation in the program within the stipulated period, delaying the start of the rest of the schools in the program. Two school recruitment periods will be stipulated to reach the desired sample size within the same academic year. Participants will be blinded, only knowing that they will be participating in a cannabis prevention project.

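### Baseline cannabis use is both an outcome wave and a covariate in the effect model, and no condition-by-time contrast is fixed, so the reported effect can be too small or too large

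*Protocol article*

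**What the plan says.** All the relevant text is in the Protocol article, mostly under Effectiveness and process evaluation.

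- Purpose of the model: "a multilevel approach will be used to assess the effects of the intervention on the behavior of cannabis use".
- Level 1: "The first level will be repeated measures within the participants (baseline and two follow-up measurements". Above it, "the second level will be the student, the third level is the class, and the fourth level is the school".
- Covariates, in the paragraph that follows directly: "Baseline cannabis will use behavior and the demographic variables described above will be included as covariates". The words are out of order, but the meaning is clear: baseline use is adjusted for.
- Term selection: "To select significant predictors and interactions, a backward deletion procedure (a = 0.05) will be used". The added restriction, itself unclear, seems to shield the components of retained terms. It does not name condition or condition-by-time as terms to keep.
- Timing: "An initial assessment (pretest) and two assessments (post-test) will be performed at six and twelve months" (Study design), and "Before starting the first session of the intervention, participants will have to complete an initial questionnaire (pre-test" (Intervention characteristics). Baseline therefore precedes any exposure.

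Nothing elsewhere in the article limits the outcome to the follow-up waves, or says which coefficient is the intervention effect.

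**The concern.** There are two standard ways to use a baseline measure. One is to adjust follow-up outcomes for it. The other is to treat it as the first outcome and read the effect from the change over time between conditions. The text combines them. In the baseline rows the covariate is then the outcome itself, and those rows can contain no intervention effect because they precede the intervention.

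This is the only analysis described for the primary outcomes. The estimate would depend on whether a pooled condition term or a condition-by-time term is reported. The two err in opposite directions on the logit scale, and a data-driven deletion step may decide between them.

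**Working it through.** The plan gives no numerical result on this point, so there is no figure of its own to reproduce.

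**Inputs.** From the article: three waves, no exposure at baseline, 1:1 allocation, 875 students per arm, and an expected 10% reduction in 30-day use. The reduction is taken here as 10 percentage points. Base rates and within-student and within-class correlations are not in the article and are assumed. The same use measure is taken to fill both roles.

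**Step 1: linear scale, complete data.** Let D0, D1, D2 be the arm differences at the three waves, and B1, B2 the within-arm slopes of each follow-up on baseline. The slope of baseline on itself is 1.

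- Pooled baseline coefficient: b = (1 + B1 + B2)/3.
- Three-wave condition effect: (D0 + D1 + D2)/3 − b·D0 = [(D1 − B1·D0) + (D2 − B2·D0)]/3.
- Follow-up-only adjusted effect: [(D1 − B1·D0) + (D2 − B2·D0)]/2.
- Ratio: (1/3)/(1/2) = 2/3, whatever the rates or correlations.

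The estimate and its cluster-robust standard error scale together, so the t statistic is unchanged.

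**Step 2: simulation.** 60 trials, 35 classes of 25 per arm, 30% baseline use, a 10-point reduction at both follow-ups, and generalised estimating equations with errors clustered by class.

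| Fit | Linear | Logit |
|---|---|---|
| Follow-ups only, baseline covariate | −0.0962 | −0.611 |
| Three waves, baseline covariate, condition effect | −0.0641 | −0.518 |
| Three waves, baseline covariate, condition × post | −0.0964 | −0.806 |
| Three waves, no baseline covariate, condition × post | −0.0964 | −0.520 |
| Baseline coefficient, follow-ups only | 0.3633 | 1.859 |
| Baseline coefficient, three waves (condition-effect fit) | 0.5755 | 3.033 |

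The linear figures match Step 1: (1 + 2 × 0.3633)/3 = 0.5755, and 0.0962 × 2/3 = 0.0641. On the logit scale the pooled effect is 0.518/0.611 = 0.85 of the follow-up effect. The interaction is 0.806/0.611 = 1.32 times that effect. The two three-wave logit estimates that keep the covariate differ by a factor of 0.806/0.518 = 1.56.

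**Step 3: other assumed settings.**

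- 16 schools, about 15% use, 300 trials: linear −0.0361 against −0.0542 (0.667); logit −0.392 against −0.452 (0.87).
- 16 schools, about 24% use, 150 trials: linear −0.056 against −0.084 (0.667); logit −0.496 against −0.606 (0.82); logit interaction −0.78 (1.29 times); baseline log-odds coefficient 1.63 rising to 2.90.
- A further run: linear 0.667; logit about 0.81; logit interaction −0.74 against −0.60 (1.23 times), and −0.54 without the covariate.

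**Step 4: student-level variance.** With B1 = B2 = B, the residual covariance between a baseline row and a follow-up row is (1 − b)(B − b) times the baseline variance. From Step 2 this is 0.4245 × (0.3633 − 0.5755) = −0.090 times that variance. A random student effect needs positive covariance, so its estimate is pushed down. In a fitted mixed model it fell from 0.030 (follow-ups only) to about 0.

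**Step 5: the test.** In 300 trials with 16 schools, about 17% use and school-clustered errors, the linear t statistics agreed to within 0.0005. Type I error was 6.7% in both fits and power 94.3% in both. Logistic type I error was 7.7% and 8.0%, and power 95.0% and 94.7%. In the further run of Step 3, t was −4.63 in both fits.

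**The case against.** The strongest reply is that the article never says the effect is a condition term averaged over three waves. It mentions interactions, and its outcomes are tied to 6 and 12 months. A condition-by-time reading removes the dilution on the linear scale. That much stands, and it means a bias toward zero cannot be asserted without qualification. But no such term is named or protected. On the logit scale, the natural one for prevalences, the term is exaggerated if the covariate stays.

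The article also lists lifetime, 12-month and 30-day use without saying which is the covariate. If it differed from the outcome, the coupling would be looser and the sizes above would not apply. The text draws no such distinction.

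An unseen analysis plan may settle the model. Even so, the published text states a double use rather than leaving a detail open.

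Four stronger readings are tempting, and the documents do not support them:

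- *Baseline rows are predicted perfectly or carry no residual error.* One coefficient is shared over waves and is below 1. Baseline residual variance was 0.031 to 0.034 against 0.12 to 0.14 at follow-up in one set of fits, and 0.048 against 0.162 in another: smaller, but not nil.
- *The adjusted baseline difference is zero by construction.* It is (1 − b)·D0, zero only in expectation. Its standard deviation across simulated trials was 1.3 points.
- *The standard errors are wrong.* Step 5 shows no such fault in cluster-robust fits.
- *The effect is always biased toward zero.* The direction depends on which term is reported.

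**Conclusion.** The point holds as a fault in the size of the estimate and should be settled before analysis. With the same measure in both roles, a pooled three-wave condition effect is two thirds of the follow-up effect on the linear scale, so 10 points would be reported as about 6.7. This ratio is algebraic for complete, balanced data. On the logit scale the pooled effect is about 0.81 to 0.87 of the follow-up effect, and a condition-by-time estimate about 1.23 to 1.32 times it. These ranges rest on assumed rates and correlations. The baseline coefficient is inflated and the student-level variance distorted.

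The cluster-robust test of no effect is essentially unchanged, so nothing here shows an invalid significance test. The full four-level logistic random-effects model was not fitted, so its behaviour is inferred from the simpler fits.

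**What to change.** State one of two models before analysis:

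1. Level-1 outcomes are the 6- and 12-month measures only, with baseline use as a covariate. Include condition, time and condition-by-time, and report the condition contrast at each follow-up.
2. Level-1 outcomes are all three waves, with baseline use removed from the covariates. The pre-specified condition-by-time contrasts are the effect estimates.

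In both, exempt condition and condition-by-time from backward deletion. Under the first, name the use measure that serves as the baseline covariate for each outcome. The choice should be made in advance because the two need not give the same log odds ratio (−0.61 and −0.52 in the simulation of Step 2).

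The cost is a sentence or two in the protocol or analysis plan. Design, questionnaires and data collection are unaffected.

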**Methods:**

The Alerta Cannabis research project consists of design, implementation, and evaluation. In the first phase, a computer-tailored eHealth program (Alerta Cannabis) is developed based on the I-Change Model, an integrated model based on three main behavioral change processes: awareness, motivation, and action. This program consists of four 30-minute sessions that will provide culturally adapted and personalized advice to motivate students not to use cannabis through text feedback, animations, and gamification techniques. This phase will also include usability testing. In the implementation phase, secondary school students from Western Andalusia, Spain (Seville, Cádiz, Huelva, and Córdoba) and Eastern Andalusia (Jaén, Málaga, and Granada) will be randomized to an experimental condition (EC) or a control condition (CC) for a cluster randomized clinical trial (CRCT). Each condition will have 35 classes within 8 schools. GI will receive the online intervention Alerta Cannabis. EC and CC will have to fill out a questionnaire at baseline, six months, and twelve months of follow-up. In the last phase, the effect of Alerta Cannabis is evaluated. The primary outcomes are the lifetime prevalence of cannabis use and its use in the last 30 days and at 6 months. At 12 months of follow-up, the prevalence in the last 12 months will also be assessed. The secondary outcome is the intention to use cannabis.

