A possible limitation of this study could be related to the exclusion criteria related to the prior participation in a specific program aimed at preventing cannabis use, which was assessed among the participant schools during the selection process. However, this criterion does not account for the potential influence of other health promotion or prevention programs within the school environment. As stated in the introduction, In Spain, the school prevention system encompasses various programs, that although not directly linked to cannabis prevention, have demonstrated evidence of impacting cannabis use. Therefore, it is challenging to control for their influence. Furthermore, comparing selected schools based on the number, type, and extent of their prevention programs poses a challenge due to the high variability between regions and within schools. In addition, although there are other possible factors that could influence cannabis use, such as the use of other substances, mental health issues, or other life stressful events, we made the decision to focus solely on general sociodemographic factors to avoid overwhelming adolescents during the completion of the questionnaire. However, we recognize that these factors could act as confounders, and their consideration would be valuable in understanding and explaining why some adolescents may respond more positively to the tested intervention.

In conclusion, it is imperative to continue promoting a culture of evidence-based prevention and to develop efficacy evaluation protocols for prevention programs. By addressing these challenges and conducting further research, we can advance our understanding of effective strategies for substance abuse prevention in school settings. The findings will contribute to the development of future interventions to prevent cannabis use in adolescents. Providing an analysis of the effect and process of a specific program to prevent cannabis use, since the prevention programs of the service portfolio of the Andalusian health system to date have not been evaluated in terms of effect. This program could be a helpful tool for school nurses [60] in charge of implementing prevention programs in the Andalusian context. If the program proves to be effective, the ultimate goal would be national and eventually international implementation.

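### If the four-level model is fitted with random intercepts only and change from baseline is tested, school randomisation drops out of the standard error; the plan should name the contrast, give baseline one role and add cluster-by-wave terms

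*Protocol article*

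**What the plan says.** All of the analysis text is in the protocol article, Effectiveness and process evaluation.

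- **Lowest level.** "The first level will be repeated measures within the participants (baseline and two follow-up measurements"). Baseline is therefore among the outcome measurements.
- **Upper levels.** "the second level will be the student, the third level is the class, and the fourth level is the school". No random wave slope, school-by-wave or class-by-wave component is named, and none is excluded.
- **Baseline again.** "Baseline cannabis will use behavior and the demographic variables described above will be included as covariates". Baseline use is thus both an outcome and a covariate.
- **Choice of terms.** "To select significant predictors and interactions, a backward deletion procedure (a = 0.05) will be used". Interactions are mentioned, but condition-by-wave is not named as the intervention effect.

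On the design, Study design says that "condition will be randomized at the school level" and that "The allocation ratio will be 1:1 using an online randomization system". The abstract (Methods) adds: "Each condition will have 35 classes within 8 schools".

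**The concern.** With baseline in the outcome vector, a condition main effect would average in a wave at which the programme cannot yet have acted. The natural intervention effect in such a model is condition-by-wave, that is, the difference between arms in change from baseline.

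A random intercept for a school or class takes one value at all three waves, so it cancels from any change within students. If the upper levels carry intercepts only, the change contrast is tested against the student-level residual alone. Any movement between waves that a whole school or class shares is then counted as independent student noise, although the school is the unit of randomisation and there are only 8 per arm.

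The confidence interval for the programme effect would then be too narrow, and an ineffective programme would be declared effective too often. A small-sample correction to the degrees of freedom would not cure this, because the variance component that matters is not in the model.

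**Working it through.** **Inputs from the protocol article.** 8 schools and 35 classes per arm (abstract, Methods); 875 students per arm, which equals 35 × 25, and an ICC of 0.2 (Sample size); α = 0.05 (Sample size), taken as two-sided.

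**Assumptions.** Total variance 1. Cluster variance split equally between school and class. Student autocorrelation 0.5. Cluster autocorrelation (CAC) 1.0, 0.9 or 0.8. ICC 0.02, 0.05 or 0.2. The document gives neither autocorrelation nor the split.

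**Formulas for the 12-month-minus-baseline contrast, no true effect.**

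- School-by-wave variance v_s = class-by-wave variance v_c = (ICC/2) × (1 − CAC)
- Residual variance v_e = (1 − ICC) × 0.5
- True variance = 4 × (v_s/8 + v_c/35 + v_e/875)
- Variance reported by the intercept-only model = 4 × (v_s + v_c + v_e)/875
- Rejection rate = 2 × [1 − Φ(1.96/R)], where R is the square root of true over reported variance

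The factor 4 is two waves times two arms.

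**Nominal level first.** At CAC 1.0, v_s = v_c = 0, so R = 1 and the rejection rate is 5.0% at any ICC. This matches the plan's α.

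**One case in full: ICC 0.2, CAC 0.8.**

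- v_s = v_c = 0.1 × 0.2 = 0.02; v_e = 0.8 × 0.5 = 0.4
- True: 4 × (0.02/8 + 0.02/35 + 0.4/875) = 4 × (0.002500 + 0.000571 + 0.000457) = 0.01411
- Reported: 4 × 0.44/875 = 0.00201
- Ratio 7.02; R = 2.65; 1.96/2.65 = 0.74; rejection rate 45.9%

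**Type I error, intercepts only, change from baseline tested.**

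| ICC | CAC 1.0 | CAC 0.9 | CAC 0.8 |
|---|---|---|---|
| 0.02 | 5.0% | 8.2% | 11.4% |
| 0.05 | 5.0% | 13.2% | 20.2% |
| 0.2 | 5.0% | 33.6% | 45.9% |

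The split matters. At ICC 0.2 and CAC 0.8 the rate is 27.2% if all cluster variance lies at class level and 55.2% if all lies at school level.

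**Simulation check.** A balanced Gaussian simulation (2,000 runs; 8 schools × 4 classes × 27 students per arm) gave 9.4%, 14.3% and 35.5% at CAC 0.9 and 11.7%, 20.8% and 45.4% at CAC 0.8, for ICC 0.02, 0.05 and 0.2. In the same runs:

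- a test of school mean change on 14 degrees of freedom rejected in 4.4% to 5.8%;
- a baseline-adjusted comparison of the average follow-up rejected in 4.4% to 5.7%;
- a baseline-adjusted comparison at 12 months alone, with school intercepts but no school-by-wave term, rejected in 4.0% to 7.8%.

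**Baseline in both roles.** A covariate that is constant over waves also cancels from a within-student contrast. A simulation of this literal version at CAC 0.9 gave 7.3%, 10.5% and 31.7% at the three ICCs, so keeping baseline as a covariate as well does not rescue the test.

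**The case against.** The strongest reply is that the protocol article states neither premise. Listing four levels does not say that each carries an intercept only, and an article may leave the random-effects detail to a fuller document. Nor is condition-by-wave named as the test. The covariate sentence supports a baseline-adjusted follow-up comparison, which keeps close to 5%. Both points stand, so the concern is conditional.

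A reader might infer from the four levels that the trial's test is invalid as planned, with a false-positive rate well above 5%. The document does not support that, for three reasons:

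- The inflation is zero if cluster effects are stable, and no autocorrelation is given.
- The Discussion says that comparing schools on their prevention programmes is hard "due to the high variability between regions and within schools". That describes differences, not change between waves, and a school intercept absorbs stable differences between schools.
- The ICC of 0.2 comes from a power statement framed around 60 practices per group, which does not match 35 classes within 8 schools. It is weak evidence about these schools.

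The added random effects may also be estimated at zero or be unstable with binary outcomes and 16 schools, which is why a fallback is needed.

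What the reply does not remove is that the text keeps baseline in the outcome vector. The favourable reading requires taking it out. Fitted as listed, the model can give the wrong standard error for the contrast that the baseline wave creates.

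**Conclusion.** The concern holds conditionally. If the listed levels are random intercepts and change from baseline is tested, school randomisation does not enter the standard error. Type I error is then 5% only with perfectly stable cluster effects. Under the assumed autocorrelations of 0.9 and 0.8 it runs from about 8% to 11% at ICC 0.02 up to 34% to 46% at ICC 0.2. These figures rest on the equal school/class split, a student autocorrelation of 0.5 and a Gaussian approximation, so they show direction and order of size for binary outcomes, not a forecast.

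If baseline is a covariate only, the problem is small: near 5% for the average follow-up effect and up to about 8% at 12 months alone. The plan does not say which analysis it means, and the choice decides whether the error rate is protected. It is worth correcting before analysis, but the text does not show that the test is already invalid.

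**What to change.** In Effectiveness and process evaluation, name the tested contrast and give baseline one role. Either:

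1. keep baseline as an outcome measurement, remove baseline use from the covariates, test condition-by-wave, and add random school-by-wave and class-by-wave effects; or
2. use only the 6- and 12-month measurements as outcomes, with baseline as covariate and random school, class and school-by-wave effects.

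In both cases, use between-school degrees of freedom, and state in advance that if the fit is singular the analysis falls back on a comparison of school mean changes across the 16 schools.

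The cost is a short change of wording plus a rule for the fallback, with no new data. Confidence intervals will be wider, and the reported estimator may turn out to be the fallback.
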